#### **4. Potential risk and benefits for participants.**

For this study, AEs will include symptoms reported by the patient and abnormal measures of clinical importance noted by study staff. AEs will also include breaches of confidentiality; reports of current and/or intended physical harm to persons (including current and/or intended abuse of children or elders, or an investigation of such allegations(s)); as well as reports of discomfort from or dissatisfaction with assessment procedures, embarrassment in disclosing sensitive personal information, or dissatisfaction with intervention activities. Each AE will be classified by the study investigators as serious or non-serious and appropriate reporting procedures followed. For purposes of this data safety plan, SAEs are defined as any fatal event, any immediately life-threatening event, any permanent or substantially disabling event, and any event that results in hospitalization. Overall, direct-acting antiviral (DAA) regimens are extremely well tolerated, with only mild to moderate side effects. The most common adverse effects include headache, fatigue, diarrhea, nausea, pharyngitis, and insomnia, with fewer than 1% of patients in clinical trials stopping the medication because of adverse effects. Reactivation of hepatitis B virus (HBV) infection has been described during DAA treatment, thus this study will screen and exclude persons positive for HBsAg. Other than these risks associated with standard clinical care for HCV infection, the potential additional risk to study participants is minimal and includes breach of confidentiality and the discomfort of fingersticks and venipuncture. The benefits to participants include improved access to HCV virologic testing and effective treatment.

#### **5. Plans for interim analysis.**

At least quarterly during one of its weekly meetings, the Executive Committee will review AE and SAE reports for safety issues, recruitment attainment (including participants screened, impact of eligibility criteria, refusal, and expected accrual rate), balance of key characteristics on randomization, follow-up adequacy (including follow-up rates and on-time rates (within 2 weeks), and missing data on key variables (including HCV viral load). This information will be compiled and shared with the DSMB at its periodic meetings. One formal interim analysis for efficacy is planned for when half of enrolled participants have been evaluated for sustained virologic response at 12-weeks post-treatment (SVR12).

#### **6. Trial stopping rule.**

Early termination for efficacy is based on the difference between study groups on the proportion achieving SVR12. It is computed using the O'Brien-Fleming estimate of the alpha-spending function for one interim (at

50% at 12-weeks post-treatment) and one final test of significance. At the interim look, if the difference in proportion of completing treatment achieves a p-value of 0.003 or less, enrollment will stop due to efficacy. If the study continues to completion, the final p-value for testing adjusted for the interim look will be 0.047. At the interim look, we will also consider stopping for futility. This decision will be based on conditional power (Proschan, Lan, Wittes, 2010). Using the interim data, conditional power will be computed under two conditions: a) conditional power under the originally-hypothesized estimates, and b) conditional power under the observed data. If both estimates of conditional power fall below 0.10, then then we consider stopping the study for futility. While a low conditional power will inform the decision to stop the study, the final decision to terminate the trial will consider other factors, such as participant engagement and care delivery.

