### E. Analysis Plan.

**Primary outcomes** will be the proportion of PWID who initiate DAA treatment, achieve sustained virologic response at 12-weeks post-treatment (SVR12), and report no syringe sharing in the prior 30 days at follow-up. We hypothesize that, compared with EUC, mobile tele-HCV care will be associated with:

H1: higher rates of DAA treatment initiation,

H2: higher rates of sustained virological response 12-weeks post treatment (SVR12 or cure), and

H3: lower rates of syringe sharing behavior among rural HCV-infected PWIDs

Secondary outcomes will include HBV and HAV vaccination series completion rates, initiation of MOUD and ED visits, as well as health-related quality of life (HRQOL) and substance use.

**Preliminary Analyses:** Initial data analysis will describe the distribution of all outcomes by study group. Continuous measures will be reported using means, standard deviations, medians and percentiles. Categorical measures will be reported using frequencies and percentages. Rather than testing for baseline covariate imbalance, stratified analyses will be conducted for baseline covariates that are known to be strongly associated with outcomes, as well as those that show imbalance on inspection.

**Primary outcome analyses.** We will apply ICH-E9 guidelines for statistical analysis and the CONSORT statement for reporting of findings. Since Aims 1 and 2 examine the effectiveness of the intervention by comparing proportions in the two study groups, we will apply the same statistical approach. For the univariable approach, study groups will be compared using Pearson's chi-square or Fisher's exact test. Stratification and adjustment for relevant baseline covariables will be accomplished with logistic regression. In

these models, study group and other categorical measures will be represented with indicator variables. Continuous explanatory variables will be evaluated to verify linearity of their logit and, if not, they will be rescaled. Model fit will be examined and final results will be expressed as odds ratios and adjusted proportions each with 95% confidence intervals. Significance testing will be conducted at a critical level of 5%.

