either measure (i.e., 77% vs. 58% for sharing any equipment, and 66% vs. 47% for sharing syringes only) for a two-sided test in the difference in proportions at a critical level of 5%. The 19-point difference for these outcomes yields an OR of about 2.4, which equates to a medium effect size (approximate Cohen's  $d = 0.48$ ).

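### The efficacy stopping threshold is applied to treatment completion, although the same rule says early stopping rests on SVR12

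*Protocol*

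**What the plan says.** Three statements in the protocol's Data and Safety Monitoring part bear on the efficacy stop.

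- Section E.5, Plans for interim analysis: "One formal interim analysis for efficacy is planned for when half of enrolled participants have been evaluated for sustained virologic response" at 12 weeks post-treatment.
- Section E.6, Trial stopping rule, first sentence: "Early termination for efficacy is based on the difference between study groups on the proportion achieving SVR12". The boundary is then said to be "computed using the O'Brien-Fleming estimate of the alpha-spending function for one interim" and one final test.
- Section E.6, operative sentence: "if the difference in proportion of completing treatment achieves a p-value of 0.003 or less, enrollment will stop due to efficacy". If the trial continues, "the final p-value for testing adjusted for the interim look will be 0.047".

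The Analysis Plan (section E of the Approach) names three primary outcomes: DAA initiation, SVR12 and no syringe sharing. Its secondary outcomes are completion of the HAV and HBV vaccine series, MOUD initiation, ED visits, health-related quality of life and substance use. Completion of DAA treatment is in neither list.

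**The concern.** The sentence that tells the DSMB what to do names a different variable from the one on which the rule says it rests. A participant can finish treatment and not be cured, or finish and miss the 12-week blood draw. Completion also depends heavily on initiation, which is a separate hypothesis (H1).

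The instruction is directive: enrollment will stop. The futility rule in the same section is softer, speaking only of considering a stop and weighing other factors. Taken literally, a binding efficacy stop could therefore follow from a difference in completion without evidence on cure.

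The pair 0.003 and 0.047 presupposes the same hypothesis at both looks. If the interim tests completion and the final tests SVR12, a completion p-value of 0.003 says nothing about the probability of stopping for efficacy when cure rates do not differ.

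**Working it through.** **1. Are the two terms the same variable in this protocol?** No.
- The section on determining SVR12 and reinfection by DBS (Approach, F) defines SVR12 as undetectable HCV RNA on a venous sample taken twelve weeks after treatment completion.
- The sample size text treats completion of therapy as its own point of attrition, separate from initiation.
- The follow-up schedule has an end-of-treatment visit and a separate visit 12 weeks later.
- No section defines completion as another name for SVR12.

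**2. Is the threshold itself right?** Yes, for either variable. Inputs are an overall two-sided alpha of 0.05 and an information fraction t = 0.5. The Analysis Plan states "Significance testing will be conducted at a critical level of 5"%. Two-sidedness is stated for the sharing outcome and assumed here for SVR12.
- Lan-DeMets O'Brien-Fleming-type spending: 4 × [1 − Φ(z₀.₉₈₇₅ / √t)] = 4 × [1 − Φ(2.2414 / 0.7071)] = 4 × [1 − Φ(3.170)] = 0.00305.
- This reproduces the stated 0.003. The formula contains only alpha and t, so naming SVR12 in the sentence does not alter the boundary.
- The exact final level to go with it would be 0.0490. The stated 0.047 is slightly conservative (0.003 with 0.047 gives an overall alpha of about 0.048) and is not at issue here.

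**3. How often would each rule cross at the interim?** Half of 220 is 110, so n = 55 per arm. The critical value for two-sided p = 0.003 is z = 2.968. The probability of crossing in favour of MTC is

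Φ{[(p_M − p_E) − z × SE₀] / SE₁},

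with SE₀ = √[2 p̄(1 − p̄)/n] and SE₁ = √{[p_E(1 − p_E) + p_M(1 − p_M)]/n}.

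Planned initiation is 50% (EUC) and 70% (MTC). The protocol gives no completion rates, so 95% and 90% completion among initiators are assumptions:
- 95%: 0.95 × 50% = 47.5% and 0.95 × 70% = 66.5%
- 90%: 0.90 × 50% = 45% and 0.90 × 70% = 63%

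| Variable tested | EUC vs MTC | SE₀ | SE₁ | Argument of Φ | Crosses |
|---|---|---|---|---|---|
| Completion, 95% of initiators (assumed) | 47.5% vs 66.5% | 0.0944 | 0.0927 | (0.190 − 0.280)/0.0927 = −0.97 | 16.5% |
| Completion, 90% of initiators (assumed) | 45% vs 63% | 0.0950 | 0.0935 | (0.180 − 0.282)/0.0935 = −1.09 | 13.7% |
| SVR12 at the planned ITT rates | 30% vs 48.5% | 0.0931 | 0.0914 | (0.185 − 0.276)/0.0914 = −1.00 | 15.9% |
| SVR12 equal in both arms | no difference | equal to SE₁ | equal to SE₀ | −2.97 | 0.15% |

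**4. What would equal SVR12 alongside unequal completion require?** Suppose SVR12 were 30% in both arms and all cures occurred among completers. Cure among completers would then be 30/47.5 = 63% in EUC but 30/66.5 = 45% in MTC. The protocol's as-treated assumption runs the other way: 40% in EUC and 65% in MTC among those who initiate.

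**The case against.** The strongest reply is that this is a slip of wording whose meaning can be recovered. The rule's first sentence names SVR12, the boundary sentence that follows refers back to it, and the interim is timed by SVR12 evaluation. A look at completion would not need to wait until 12 weeks after treatment. The protocol is loose elsewhere too, calling ITT SVR12 treatment success in the sample size text. The DSMB is also charged with approving the interim analysis plan and reviewing the detailed monitoring plan before data collection, which is a natural point to catch the phrase.

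Most of this stands: SVR12 is very probably the intended endpoint, and the DSMB review lowers the chance that the sentence would be acted on unexamined. Neither corrects the text. A stopping rule has to be executable as written, and the sentence that executes this one names another variable. Nor is this a detail that can be left to a statistical analysis plan, because the protocol states two different things in one section.

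A reader might go further and infer that the wording makes a false efficacy stop about a hundred times more likely, from 16.5% against 0.15%. The documents do not support that as an expected effect. The contrast assumes a 19-point gap in completion with no gap in SVR12, which the plan nowhere assumes and which needs cure among completers to be much worse in MTC. Nor do the documents support an inference that the 0.003 figure is wrong; it reproduces.

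**Conclusion.** The point holds as an internal contradiction in the protocol's only formal efficacy-stopping trigger. Two statements make SVR12 the interim endpoint; the operative sentence tests completion of treatment, which is not a listed outcome. Read literally, the stop carries no error control for the cure hypothesis.

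In size, the effect on the overall chance of stopping is small under the plan's assumptions: 13.7–16.5% for completion against 15.9% for SVR12. That comparison rests on 55 per arm, a normal approximation, the planned initiation and SVR12 rates, and assumed completion of 90–95% among initiators. Similar probabilities do not mean that the two rules would stop in the same circumstances. The risk lies where completion and cure part company, and 16.5% against 0.15% marks the outer bound of that risk.

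The correction belongs in the protocol before the interim analysis, on the strength of the contradiction in the text and not of the bounding figure.

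**What to change.** In the operative sentence of section E.6, replace the reference to completing treatment with achieving SVR12, taking all randomised participants in the interim set as the denominator. This matches the ITT definition already given in the sample size text. The 0.003 threshold stays as it is.

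Optionally, name SVR12 in the conditional-power futility rule as well. That rule states no endpoint of its own, so this is a clarification and not the correction of an error. Completion can still be shown to the DSMB descriptively.

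The cost is one phrase in the protocol and the same phrase in the Data and Safety Monitoring Plan if it is repeated there. No additional participants or data are needed.

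### The final significance level for SVR12 is misstated (0.047, where the named O'Brien-Fleming spending rule gives 0.049) and conflicts with the flat 5% in the Analysis Plan; the effect is small

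*Protocol*

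**What the plan says.** Two parts of the protocol set the level at which SVR12 is finally tested.

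- **Data and Safety Monitoring, E.5 and E.6.** "One formal interim analysis for efficacy is planned for when half of enrolled participants have been evaluated for sustained virologic response". The rule concerns one outcome: "Early termination for efficacy is based on the difference between study groups on the proportion achieving SVR12". On the boundary: "It is computed using the O'Brien-Fleming estimate of the alpha-spending function for one interim". At the interim, if the comparison "achieves a p-value of 0.003 or less, enrollment will stop due to efficacy". For a trial that runs to completion, "the final p-value for testing adjusted for the interim look will be 0.047".
- **Approach, E. Analysis Plan.** The paragraph on primary outcome analyses ends: "Significance testing will be conducted at a critical level of 5" per cent. It makes no exception for SVR12 and does not mention the interim look.

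The Analysis Plan also lists three primary outcomes, namely the proportions who "initiate DAA treatment, achieve sustained virologic response at 12-weeks post-treatment (SVR12), and report no syringe sharing in the prior 30 days at follow-up", with separate hypotheses H1 to H3. The sample size text powers each of them separately. For sharing the test is "for a two-sided test in the difference in proportions at a critical level of 5" per cent, and SVR12 is powered with no allowance for the interim look. No section says whether one, some or all of the three hypotheses must succeed for the model to be called effective.

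**The concern.** A group-sequential boundary is a matched pair. Once the spending function, the information fraction and the overall alpha are fixed, the interim and final nominal levels both follow. Here the interim figure agrees with the named function and the final figure does not, so the stopping rule contradicts its own method.

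The protocol also gives two final thresholds for the one outcome that can stop the trial early. A final SVR12 p-value of 0.048, for example, would fail under the stopping rule and pass under the Analysis Plan. That choice should not be open once results are known, least of all in an open-label trial.

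The missing success rule across H1 to H3 is a separate and conditional matter. It has consequences only if a positive result on any one outcome will be presented as showing that the model works.

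**Working it through.** **Inputs.** From the stopping rule and interim plan: O'Brien-Fleming spending, one look at information fraction t = 0.5, interim p 0.003, final p 0.047, endpoint SVR12. From the Analysis Plan: critical level 5%; 110 participants per group; SVR12 of 30% against 48.5% by intention to treat. Assumption: overall two-sided alpha of 0.05 (0.025 per side), in line with the two-sided 5% in the sample size text.

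**Step 1. Reproduce the interim level.** The Lan-DeMets O'Brien-Fleming function spends, per side, 2 × [1 − Φ(z₀.₉₈₇₅ / √t)].
- z₀.₉₈₇₅ = 2.2414, and 2.2414 / √0.5 = 3.1698.
- 1 − Φ(3.1698) = 0.000763. Per side: 2 × 0.000763 = 0.001525. Two-sided: 0.00305.

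This matches the stated 0.003. The interim critical value is z = 2.963.

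**Step 2. Solve for the final level.** The statistics at the two looks are bivariate normal with correlation √0.5 = 0.707. Find c such that P(|Z₁| ≥ 2.963 or |Z₂| ≥ c) = 0.05. The solution is c = 1.969, a two-sided nominal p of 0.0490. Entering exactly 0.003 at the interim also gives 0.0490.

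**Step 3. Look for a rule that gives 0.003 with 0.047 at t = 0.5.**

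| Rule | Interim | Final |
|---|---|---|
| Lan-DeMets O'Brien-Fleming, 0.025 per side | 0.0031 | 0.0490 |
| Classical O'Brien-Fleming | 0.0052 | 0.0480 |
| Two-sided 0.05 spent directly | 0.0056 | 0.0478 |
| One-sided 0.05 | 0.0056 | 0.0482 |
| Pocock | 0.0294 | 0.0294 |

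None gives the stated pair. But 0.05 − 0.003 = 0.047. That is the alpha left to spend at the final look, and using it as the nominal level ignores the correlation in step 2.

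**Step 4. Overall type I error for SVR12, with interim level 0.003.**

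| Final level | Critical z | Overall alpha |
|---|---|---|
| 0.047 | 1.986 | 0.0480 |
| 0.049 | 1.969 | 0.0500 |
| 0.050 | 1.960 | 0.0510 |

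**Step 5. Effect on SVR12 power.** Power = Φ[(d − z × SE₀) / SE₁], with d = 0.185, pooled SE₀ = √(2 × 0.3925 × 0.6075 / 110) = 0.0658, and SE₁ = √(0.30 × 0.70 / 110 + 0.485 × 0.515 / 110) = 0.0647. This treats the final test as a single test at the level shown.
- At 0.05: 80.7%, which reproduces the protocol's figure of about 80%.
- At 0.049: 80.4%.
- At 0.047: 79.9%.

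**Step 6. Three primary outcomes, conditional.** If any one success at 5% counts as a positive trial, and no outcome has a true effect:
- Independent tests: 1 − 0.95³ = 0.143.
- Common correlation of 0.3, 0.5 or 0.8 between the test statistics: about 0.136, 0.125 and 0.098.

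The protocol gives no correlation, so these values are assumptions. If all three must succeed, each can be tested at 5% without adjustment.

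**The case against.** Four points can be made for the plan.

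- **0.047 is on the safe side.** A slightly strict final level fixed in advance still controls type I error: overall alpha is 0.048. This stands. A reader might infer from the wrong boundary that the false-positive rate for SVR12 is inflated; under the stopping rule as written it is not. What remains is that the figure does not follow from the named method.
- **The specific rule may be meant to override the general one.** The Analysis Plan speaks for all primary outcomes, two of which have no interim efficacy test, and the stopping rule speaks for SVR12. That is a reasonable reading, but no cross-reference says so, and SVR12 is powered with no allowance for the interim look. Even on the worse reading, overall alpha is only 0.051.
- **Multiplicity is often left to the statistical analysis plan.** This stands as far as it goes. A 5% level for each outcome does not rule out a hierarchy, since a fixed sequence also tests each step at 5%.
- **The any-one-of-three reading is not in the protocol.** This also stands. A reader might infer that the trial's false-positive rate is 13% to 14%. The documents do not support that as a fact: they state no rule that one success suffices, and the background section speaks of testing, treatment and syringe access together as one approach. The figure also leans towards independence, although the background links HCV treatment to less syringe sharing, so positive correlation is plausible.

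**Conclusion.** Two statements are wrong as written. The final SVR12 level should be 0.049 for the spending function, look and interim level that the protocol names. The stopping rule and the Analysis Plan also give different final levels for SVR12. Both conclusions rest on an overall two-sided alpha of 0.05 and an interim at 50% information.

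The practical effect is small. Overall alpha lies between 0.048 and 0.051 whichever figure is used, power changes by about half a percentage point (79.9% to 80.4%), and the conflict decides the result only if the final p-value falls between 0.047 and 0.050.

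The point on three primary hypotheses is secondary and conditional: about 10% to 14% family-wise error if any one success is to support the effectiveness claim, and no problem if all three are required. It is a request to state the rule, not a demonstrated inflation. Overall severity is minor to moderate.

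**What to change.** 1. In the Trial stopping rule, give the final level for SVR12 once, as two-sided 0.049, with the interim level of 0.003 unchanged.
2. In the Analysis Plan, keep 5% as the general level and cite 0.049 as the exception for SVR12.
3. State the success rule for H1 to H3. If all three are required, say so and make no adjustment. If any one suffices, use a fixed sequence compatible with the interim look, for example SVR12 first at 0.003/0.049, then the other two in a stated order, each at overall 0.05. Say how those two would be tested if the trial stops at the interim, so that 0.05 still holds for each over both looks.

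Two alternatives fit less well. Putting H1 ahead of SVR12 clashes with an interim efficacy test made on SVR12 alone. Holm would replace the 0.049 level and cost power: at a Bonferroni level of 0.0167, shown for scale, SVR12 power is 66.4% against 80.7% at 5%.

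Items 1 and 2 cost only wording. In a fixed sequence SVR12, tested first, loses no power, but later outcomes can be claimed only if the earlier ones succeed. The choice should be made before comparative results are seen.

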## 7. Conflict of interest.

The researchers involved in this study do not have any known conflict of interest issues in this Data and Safety Monitoring Plan. The IRB will verify that no conflicts of interest exist as part of their review. Given the nature of the study, it is unlikely that an unmanageable conflict of interest could arise. If a conflict of interest emerges that cannot be rectified, the conflicted staff will be reassigned. DSMB members will not include anyone with a conflict of interest.

